## Abstract

**Background:**

Smoking cessation is beneficial for our health at any point in life, both in healthy people and in people already suffering from a smoking-related disease. Any help to quit smoking can produce considerable benefits for Public Health. The purpose of the present study is to evaluate the efficacy of the CO-oximetry technique together with brief advice in smoking cessation, in terms of reduction of the number of cigarettes or in the variation of the motivation to quit smoking at month 12 compared with brief advice alone.

**Methods/Design:**

Randomised, parallel, single-blind clinical trial in a primary health care setting in Majorca (Spain). Smokers in contemplation or pre-contemplation phase will be included in the study. Exclusion criteria: Smokers in preparation phase, subjects with a terminal illness or whose health status does not allow them to understand the study or complete the informed consent, and pregnant or breastfeeding women. The subjects will be randomly assigned to the control group (CG) or the intervention group (IG). The CG will receive brief advice, and the IG will receive brief advice together with a measurement of exhaled CO. There will be follow-up evaluations at 6 and 12 months after inclusion. 471 subjects will be needed per group in order to detect a difference between groups ≥ 5%. Primary outcome: sustained smoking cessation (at 6 and 12 months) confirmed by urine cotinine test. Secondary outcomes: point smoking cessation at 6 and 12 months both confirmed by urine cotinine analysis and self-reported, reduction in cigarette consumption, and variation in phase of smoking cessation.

**Discussion:**

CO-oximetry is an inexpensive, non-invasive, fast technique that requires little technical training; making it a technique for risk assessment in smokers that can be easily applied in primary care and, if proven effective, could serve as a reinforcement aid in smoking cessation intervention activities.

**Trial Registration:**

Current Controlled Trials ISRCTN67499921

## Background

Tobacco smoking is the first cause of avoidable death in industrialised countries [1]. It has been known for many years that the negative effects of tobacco smoking on health are numerous [2,3]. Tobacco smoking is involved in the appearance of different types of cancer. It is also the main risk factor for cardiovascular disease, the most common known cause of chronic obstructive pulmonary disease, and many other health problems. Despite wide knowledge on the subject, the prevalence of tobacco smoking is still high. According to the 2006 National Health Survey, 31.56% of adult men and 21.51% of women are daily smokers, of whom 79% of men and 70% of women smoke more than 10 cigarettes per day.

Smoking cessation is beneficial for health at any point in life, both in healthy people and in people already suffering from a smoking-related disease [4]. However, smoking cessation is not an easy task, given that nicotine is a drug that generates great addiction [5].

According to article 12 of the Spanish Act 28/2005 (art. 12 Ley 28/2005) based on health measures for tobacco smoking and the regulation of its sale, supply, consumption and the advertising of tobacco products, the Spanish public Administrations are to promote the development of health programmes for smoking cessation in the Spanish Health System, especially in Primary Care. Likewise, National Health System strategies for cancer, ischemic cardiopathy and chronic obstructive pulmonary disease include reducing the prevalence of tobacco smoking amongst their objectives.

Although many smokers claim to have quit smoking on their own [6], others require specific help. Primary care doctors and nurses see most of the smokers at least once a year in their practice and have an excellent opportunity to diagnose tobacco smoking, evaluate the motivation behind it, and help them quit smoking. There is growing evidence on how healthcare professionals can help smokers end their addiction through pharmacological and non-pharmacological therapies [7]. The latter include: brief advice given by a doctor or a nurse, the delivery of self-help materials or more complex or intensive interventions based on motivational interviews and cognitive-behavioural techniques for psychological support, sometimes combined with pharmacological therapies [8].

The majority of non-pharmacological interventions for smoking cessation use the so-called transtheoretical model of change described by Prochaska and DiClemente at the beginning of the 90s [9]. According to this model, the smoker goes through a series of phases during his/her smoking cessation process: pre-contemplative (the smoker does not contemplate quitting smoking), contemplative (the smoker begins to be unhappy with his/her addiction and starts thinking about quitting smoking within the next 6 months), preparative (the smoker is prepared to quit smoking), smoking cessation and the eventual relapses that re-start the cycle.

The brief advice given by a healthcare professional can achieve between 1–3% smoking cessations after 6 months, taking into consideration that an additional 2–3% manage to quit smoking without help. Therefore, this measure is moderately effective, although it has a great impact across the population [10] and the percentage can be increased if the advice is not as brief and/or if it is accompanied by self-help and/or follow-up materials [11]. In order to increase the rates of smoking cessation by means of brief advice, another strategy could be the evaluation of the physical effects of smoking using physiological measures that offer the smoker some feedback on the effects of smoking, as happens with hypertensive patients and blood pressure readings [12].

These interventions are based on the hypothesis that one of the reasons why people continue smoking, in spite of knowing the harmful effects of tobacco, is that they underestimate the personal risk of becoming ill because of it. In this sense, the interventions will offer motivational feedback to promote awareness of the risk [13]. It has been suggested that some smokers who manage to quit smoking are more aware of the adverse effects of tobacco or to have had their health seriously compromised [14,15].

Three different types of feedback have been established: the first type analyses biomarkers of exposure to tobacco (nicotine, carbon monoxide); the second offers information regarding the risk of tobacco-related diseases (predisposition to lung cancer according to the CYP2D6 genotype); and the third describes the harmful effects of smoking (atherosclerotic plaques or worsening of pulmonary function) [15]. Isolated studies have provided mixed results regarding the effect of biomedical risk assessment as an aid for smoking cessation. A recent systematic review [16] concludes that, due to the lack of good quality evidence, it is not possible to draw firm conclusions. The following methodological recommendations are made: use adequate sample sizes, use allocation concealment procedures, agree on a definition of “abstinence” and systematically introduce measures to biochemically confirm it and, finally, carry out analyses by intention to treat. The measurement of CO levels in exhaled air by CO-oximetry is used to evaluate the degree of smoking by the smoker given that, in general, there is a direct relationship between the levels of CO and the number of cigarettes smoked [17]. The measurement of exhaled CO is also the preferred measurement to confirm tobacco abstinence [18].

It has been observed that the measurement of CO in exhaled air in smokers could be an indicative test of immediate and future harm to their health as a consequence of smoking [19] and this could increase their motivation to stop smoking, which could lead to smoking cessation in these patients. In the review mentioned above [16], three studies that measured the direct effect of CO-oximetry on smoking cessation [20-22] were identified. Two of them were carried out in primary care settings [20,21]. No positive changes in the rate of smoking cessation were observed.

The measurement of CO levels in exhaled air by CO-oximetry is an inexpensive, non-invasive, fast technique that requires little technical training [23] making it a technique for risk assessment in smokers that can be easily applied in primary care and, if proven effective, could serve as a reinforcement aid in smoking cessation intervention activities.

Therefore, we think it would be interesting to study its possible effect on smoking cessation to a greater extent through the design of a new study incorporating the methodological recommendations given by the experts, and by providing more robust results to determine efficacy.

The purpose of the present study is to evaluate the efficacy of the CO-oximetry technique, together with brief advice, in smoking cessation at month 12 in smokers in contemplative or pre-contemplative phase compared with brief advice alone. Furthermore, the study also aims to evaluate the efficacy of the CO-oximetry technique together with brief advice in the reduction of the number of cigarettes and in the variation of the motivation to quit smoking at month 12 in smokers in contemplative or pre-contemplative phase compared with brief advice alone.

## Methods/Design

### Design and settings

A randomised, parallel, single-blind clinical trial in a primary health care setting in Majorca (Spain). The subjects will be randomised to either Control Group (CG) or Intervention Group (IG). Participants in CG will receive brief advice; participants in IG will receive brief advice with CO-oximetry.

### Study population

The study population is made up of smokers ≥18 years that attend a primary care consultation for any medical problem.

Inclusion criteria will include smokers ≥18 years in the pre-contemplation or contemplation phases described by Prochaska and DiClemente. According to the WHO, a smoker is someone who has smoked daily at least during the past month, irrespective of the amount of cigarettes he/she has smoked. A smoker in the pre-contemplation phase is someone who is not aware that he/she has a problem or thinks he/she is not able to change, does not see his/her behaviour as a reason for concern, and does not consider changes within the next 6 months. A smoker in the contemplation phase is characterised by ambivalence, he/she simultaneously considers and rejects the idea of changing, oscillates between worry and lack of worry as well as between the motivations to change or to continue without changing, and intent to change is established in the long-term without specifying when [9]. Exclusion criteria will include smokers in the preparation phase (prepared to quit smoking in a month’s time); people with a terminal illness or whose health status does not allow them to understand the study or complete the informed consent either due to mental illness or transitory psychiatric deterioration at the moment of inclusion; pregnant or breastfeeding women.

### Recruitment of subjects

Every person consulting a general practitioner (GP) or a nurse will be asked about their smoking behaviour and their attitude toward quitting smoking. To establish the patient’s phase or period of change, he/she will be asked the following: “have you ever seriously thought that you should quit smoking within 1 month?”, following the model of question used in the ISTAPS project [24].

If the subject fulfils the inclusion criteria, information on the study will be released, the subject invited to participate and, upon acceptance, will provide signed informed consent. Subsequently, the participant will be randomised to either CG or IG.

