#### Secondary outcome measures

Point smoking cessation at month 6 and/or month 12 confirmed by a urine cotinine test; self-declared smoking cessation at months 6 and 12; reduction in the number of self-declared cigarettes consumed when smoking cessation is not accomplished at months 6 and 12; variation in the phase of process of smoking cessation: from pre-contemplation to contemplation or preparation phase, or from contemplation to preparation phase, at months 6 and 12.

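### The one staging question asks about any past thought of quitting within a month, so it fits neither the protocol's present-intention phases nor its 6-month cut-point

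*Protocol article*

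**What the plan says.** All references are to the protocol article.

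- **Recruitment of subjects** gives the purpose of the item, "To establish the patient’s phase or period of change, he/she will be asked the following", and then a single question: "have you ever seriously thought that you should quit smoking within 1 month". It is described as "following the model of question used in the ISTAPS project"; that source is not reproduced.
- **Study population** admits "smokers ≥18 years in the pre-contemplation or contemplation phases described by Prochaska and DiClemente". Pre-contemplation includes a smoker who "does not consider changes within the next 6 months". Contemplation is described there as ambivalence with a long-term, undated intent. "Exclusion criteria will include smokers in the preparation phase", meaning readiness to quit in a month's time.
- **Background** defines contemplation differently: the smoker "starts thinking about quitting smoking within the next 6 months".
- **Secondary outcome measures** scores change of phase "from pre-contemplation to contemplation or preparation phase, or from contemplation to preparation phase, at months 6 and 12".
- **Intervention** requires the brief advice to suit the smoker's phase, and **Independent measures** lists phase as a baseline variable with five categories. Neither names a staging instrument.

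**The concern.** The question and the definitions ask about different things. The definitions concern what the smoker intends now, with cut-points at 6 months and 1 month. The question concerns whether a thought has occurred at any time in the past, with a 1-month horizon only.

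Phase does four jobs in this trial: it decides eligibility, shapes the advice given in both arms, describes the sample at baseline, and is the starting point of a secondary outcome tied to a stated aim (change in motivation to quit). If the item is applied as printed, the enrolled group can differ from the population the protocol names. The move from pre-contemplation to contemplation would also have no baseline from which to be scored. Forty-eight professionals in 16 centres would use this wording, so individual judgement cannot be relied on to correct it uniformly.

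**Working it through.** **1. The plan's own figure.** The sample size is not in dispute, but it was checked to see whether the point touches it. Inputs from Sample size: 5% cessation in control, a 5-point difference (so 10%), two-sided alpha 0.05, power 0.80, 10% loss.

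- Pooled normal formula: n = [1.960·√(2·0.075·0.925) + 0.842·√(0.05·0.95 + 0.10·0.90)]² / 0.05² = 435 per arm after rounding up; 435/0.90 = 484 after rounding up, within 3% of 471.
- Arcsine formula: h = 2·arcsin√0.10 − 2·arcsin√0.05; n = 2·(1.960 + 0.842)²/h² = 424 per arm; 424/0.90 = 471.1, in line with the stated 471.

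No input depends on how phase is asked, so 471 per group (942 in total) stands whatever the wording.

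**2. The question against the definitions.** The smokers who could be screened fall into five types. The phase and eligibility columns use the protocol's definitions, with the Background's 6-month horizon for contemplation. The answer column takes the question literally.

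| Type | Present intention | Past serious thought of quitting within a month | Answer | Phase by definition | Eligible |
|---|---|---|---|---|---|
| A | None within 6 months | No | No | Pre-contemplation | Yes |
| B | None within 6 months | Yes | Yes | Pre-contemplation | Yes |
| C | Within 6 months, not within 1 | No | No | Contemplation | Yes |
| D | Within 6 months, not within 1 | Yes | Yes | Contemplation | Yes |
| E | Ready within 1 month | Yes | Yes | Preparation | No |

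- A *yes* covers B, D and E. If *yes* is read as preparation, B and D are excluded although eligible.
- A *no* covers A and C, which are different phases.

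**3. Are these one fault or two?** Suppose *ever* is removed and the item asks about present thought only. B and D now answer *no*, and *yes* is left to E. Eligibility is then right, but *no* covers A to D, still a mix of pre-contemplation and contemplation. So *ever* bears on eligibility, and the missing 6-month horizon bears on the phase label. Correcting one does not correct the other.

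**4. The two definitions of contemplation.** A smoker who means to quit some day, but not within 6 months, fits the long-term, undated intent that Study population calls contemplation. The same smoker also meets that section's 6-month criterion for pre-contemplation and falls outside the Background's description of contemplation. Both phases are eligible, so enrolment is unaffected, but the phase-change outcome needs one rule.

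**5. What cannot be calculated.** The number of B and D smokers, and how often staff would stage on the literal answer alone, are not in the documents. No share misclassified can be derived.

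**The case against.** **The rest of the instrument may be in the booklet.** This is a condensed article. Phase is recorded at baseline in five categories, which one yes/no answer could not produce, so further items or clinical judgement probably exist. Patients are also asked generally about their attitude to quitting, and Study population gives qualitative criteria. This stands to the extent that nobody can say every baseline label would rest on this question. It does not remove the point: the article states affirmatively which question establishes phase, names no other, and that question conflicts with its definitions.

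**The wording is borrowed and may be a translation.** *Ever* may be a slip, and the cited source cannot be seen. The article also does not say how answers map to phases, so reading *yes* as preparation is an inference, though a natural one given that preparation is the phase with the 1-month horizon. This is why the claim is that the item *can* misclassify. A slip would still need correcting.

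**Eligibility does not need the 6-month cut.** Correct. Both phases on either side of it are eligible. Only *ever* threatens eligibility.

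**The comparison of arms is untouched.** Correct for the primary outcome. Screening precedes randomisation and applies equally to both arms.

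**Stronger readings that the documents do not support.** A reader might infer three further things.

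- *Progression is built in at follow-up, because an answer about ever can only stay or turn yes.* The item appears under recruitment. Nothing says it is repeated at 6 or 12 months, and follow-up uses a separate booklet whose items are not shown.
- *A large share of eligible smokers, say 30–70%, would be excluded.* Any such figure only restates an assumed input; the documents give no response data.
- *Those left would quit at below the planned 5%.* No figure in the documents links phase or past intention to the cessation rate.

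**Conclusion.** The point holds in a limited form. The only staging question given conflicts with the protocol's own phase definitions in two separate ways: it can exclude an eligible smoker on the strength of a past intention, and it cannot separate the two phases that are enrolled.

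The size of the first fault is unknown. It depends on how many eligible smokers have such a past intention and on whether staff take the question literally, read *yes* as preparation and stage on that answer alone. The second fault is a matter of logic and holds whatever those numbers are, provided no other staging item is used.

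The consequences are confined to who is enrolled, how far the result generalises, the phase-adapted advice and baseline phase description, and the phase-change secondary outcome. The cotinine-confirmed primary comparison is not biased by this and the stated sample size is unaffected. It should be corrected before recruitment, but it does not threaten the trial's main conclusion.

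**What to change.** Replace the question with two items on present intention:

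1. Are you seriously thinking of quitting in the next 6 months?
2. Are you planning to quit within the next month?

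State the mapping in the protocol: no to both is pre-contemplation; yes to the first and no to the second is contemplation; yes to the second is preparation, the phase Study population already excludes. Use the same two items at baseline, month 6 and month 12, so that the phase-change outcome is scored on one scale. Reconcile the contemplation definitions in Background and Study population so that the mapping and the text agree. If the booklet already holds suitable items, cite them as the staging tool and correct the wording in Recruitment of subjects.

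The cost is one extra question per contact and a change of booklet wording. Study development already plans a pilot in two centres to settle the booklet, so the change can be made there. The sample size does not need to be revised.

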### Sample size

Accepting an alpha risk of 0.05 and a beta risk of 0.20 in a bilateral contrast, and estimating a rate of loss to follow-up of 10%, 471 subjects in both the control group (CG) and the intervention group (IG) are required in order to detect a difference equal or superior to 5% between groups. A proportion of 5% smoking cessation is estimated in the CG. In total, a sample size of 942 subjects is required.

Forty-eight health care professionals from 16 health care centres will participate in the study. It is expected that each professional will include approximately 20 subjects to attain the sample size required.

### Random allocation to study arms

The randomised scheme will be carried out in blocks of 20, using a computer program. The allocation of each patient will be determined using a table of randomised numbers, and this number will be indicated on a report placed in closed, opaque envelopes sequentially numbered. Each professional will have 20 envelopes, one for each subject. The professional will not know the randomisation scheme. The socio-demographic variables, together with those on the smoking habits of the participants that decline to participate in the study, will be collected in a separate report. The inclusion period for subjects will be 12 months.

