### Intervention

The intervention applied to the CG will be brief advice, which will be serious, firm, concise, personalised and appropriate for the phase of change. The brief advice attempts to encourage subjects in a clear, firm and personalised way to quit smoking, inform more than oblige, facilitate information on the negative effects of tobacco on health, highlight the main advantages of quitting smoking and ask them to identify and examine the main obstacles when quitting smoking. Once the brief advice to stop smoking has been carried out verbally, the patients will be given a written document with advice and several guidelines. The healthcare professionals will receive training on how to give the brief advice.

In the IG, apart from giving the brief advice in exactly the same way as for the CG, a CO-oximetry test will also be carried out on each subject. Before it is performed, the basics of the test and what it measures will be explained to patients. Once the subject has properly understood how the technique works and if he/she is at an optimum moment for it to be carried out (having not smoked one hour prior to the test/having not smoked for more than 10 hours), the levels of carbon monoxide in expired air will be measured in parts per million (ppm) and recorded in the data collection booklet (DCB) and in a personal report that will be given out to the subject, together with an explanation and definition of CO-oximetry and an interpretation of the possible results.

The two interventions will be carried out by the healthcare professional including the patient in the trial, irrespective of whether he/she is a GP or a nurse. It will only be performed once, during the first visit following the inclusion of the patient into the study. Each professional will conduct one intervention or the other, depending on what intervention is assigned to the subject during randomisation.

The evaluation at months 6 and 12 will be done by a nurse blinded to patient allocation. At 6 months there will be a telephone evaluation and at 12 months an evaluation in the primary health centre.

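### Block size equals each professional's envelope set, so a recruiter who infers a 10:10 split can deduce the last allocation of a completed set, and sometimes one or more before it

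*Protocol article*

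**What the plan says.** The allocation procedure is in the protocol article under Random allocation to study arms. On the list: "The randomised scheme will be carried out in blocks of 20, using a computer program". On the envelopes: "this number will be indicated on a report placed in closed, opaque envelopes sequentially numbered", and then "Each professional will have 20 envelopes, one for each subject". The stated safeguard is "The professional will not know the randomisation scheme".

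The Intervention section makes the recruiter and the provider the same person: "The two interventions will be carried out by the healthcare professional including the patient in the trial". It adds: "Each professional will conduct one intervention or the other, depending on what intervention is assigned to the subject during randomisation". Blinding applies at follow-up: "The evaluation at months 6 and 12 will be done by a nurse blinded to patient allocation".

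Under Recruitment of subjects, consent precedes allocation: "Subsequently, the participant will be randomised to either CG or IG". Study development, item d, places collection of the baseline booklet after both consent and randomisation. The Sample size section gives 48 professionals, about 20 subjects each, and 471 per arm (942 in total). The Background reports that a systematic review recommended allocation concealment, among other measures, and says the new study is designed to take up such recommendations.

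**The concern.** Opaque, numbered envelopes stop a recruiter from reading the next allocation. They do not stop a recruiter from counting the previous ones. Anyone who has delivered CO-oximetry to some patients and advice alone to others knows the running tally. If the set is one balanced block, the tally eventually fixes what remains.

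Consent before randomisation does not remove this, because the next arm could be deduced before the next smoker is approached. Selection could then enter through who is approached and when. Eligibility turns on motivation to quit, which plausibly relates to the cessation outcome. The report on people who decline would not capture smokers who were never invited.

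A second, smaller point makes steering harder to detect afterwards. Baseline data, including phase of change and nicotine dependence, are recorded after allocation by the professional who knows it. Baseline comparisons are therefore not a clean check.

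**Working it through.** **Inputs.** Block size 20 and 20 envelopes per professional (Random allocation to study arms); 48 professionals, about 20 subjects each, 471 per arm and 942 in total (Sample size); the recruiter delivers both arms (Intervention). Two inputs are inferred: one envelope set is one block, and each block is 10:10. Both follow closely from the matching sizes and equal arms, but neither is written down.

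**The plan's own figures.** 48 × 20 = 960 envelopes against a target of 942, so 18 are spare and the mean is 942/48 = 19.6 per professional. The 471 per arm is reproduced by the arcsine formula for 5% v 10%, two-sided 0.05, power 0.80: 423.7 per arm, and 423.7/0.90 = 470.8. The sample size is not affected by this point.

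**Allocations that are determined.** The last t allocations can all be deduced when they all belong to the same arm:

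P(last t determined) = 2 × C(20 − t, 10) / C(20, 10), with C(20, 10) = 184,756.

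| Envelope | t | Calculation | Probability |
|---|---|---|---|
| 20th | 1 | 2 × 92,378 / 184,756 | 100% |
| 19th | 2 | 2 × 43,758 / 184,756 | 47.4% |
| 18th | 3 | 2 × 19,448 / 184,756 | 21.1% |
| 17th | 4 | 2 × 8,008 / 184,756 | 8.7% |
| 16th | 5 | 2 × 3,003 / 184,756 | 3.3% |

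Summed over t = 1 to 10, the expected number determined is 2 × 10/11 = 1.82 per completed set, or 1.82/20 = 9.1%.

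**Across the trial.**
- All 48 sets completed: 48 × 1.82 = 87 of 960 (9.1%).
- 942 subjects, with the 18 unused envelopes spread one per professional: a set stopped at 19 has 1.82 − 1 = 0.82 determined, so 30 × 1.82 + 18 × 0.82 = 69 of 942 (7.4%).

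**Partial predictability.** A recruiter who always guesses the arm with fewer allocations so far is right, on average, 10 + (2^20 / C(20, 10) − 1)/2 = 10 + (1,048,576/184,756 − 1)/2 = 12.34 times in 20, or 61.7% against 50% by chance.

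**Is the block simply too short?** No. The same calculation for fixed blocks of known size gives 33% determined for blocks of 4 and 25% for blocks of 6, against 9.1% for blocks of 20. The fault lies in the block boundary coinciding with the envelope set.

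**The case against.** The strongest reply is that professionals are not told the scheme. Deduction needs a professional to suppose that the set is exactly balanced and to keep a tally during a 12-month inclusion period. That stands: every figure above is conditional on the recruiter having inferred the balance. It does not dispose of the point, because a two-arm trial with equal groups that hands each recruiter exactly 20 envelopes makes 10:10 the obvious guess.

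Recruitment is also more structured than free choice. Everyone who consults is to be asked about smoking, phase is set by a standard question, and decliners are recorded. A reader might infer that recruiters may invite whom they please, and the Recruitment of subjects section does not support that. These steps limit selection without excluding it, since the same professional carries them out.

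A reader might also infer that several closing allocations of every set are known. Only the 20th is always determined, and only in a completed set; the 19th is determined in fewer than half. Finally, balance within each professional is a reasonable aim, since the same person's advice is given in both arms, and a block of 20 is already long.

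**Conclusion.** The point holds as a modest, avoidable weakness in allocation concealment. If each set is one 10:10 block and the recruiter infers it, about 69 to 87 allocations (7–9%) can be deduced in advance, and guesses throughout are right 62% of the time.

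It would be tempting to call this the main threat to the 5% v 10% comparison. The documents do not support that: they say nothing on whether any professional would steer patients, or how far steered patients would differ. For scale only, assume that every professional uses every determined allocation of a completed set and that the patients steered to the two arms differ by 5 to 10 points in underlying cessation. The shift would be 0.091 × 5 = 0.45 to 0.091 × 10 = 0.91 points, against a 5-point target. That assumes universal, deliberate steering on determined allocations; it is not an estimate. The case for acting is that the repair is cheap and that concealment is a recommendation the trial says it adopts.

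**What to change.** - **List.** Generate it with undisclosed, randomly varied block sizes whose boundaries do not coincide with the 20-envelope set, so that no set is forced to 10:10. Short fixed blocks would not serve: if their size became known they would be more predictable than the present scheme. Sealed, opaque, numbered envelopes can stay.
- **Order of steps.** Amend Study development, item d, so that the baseline booklet is completed after consent and before the envelope is opened. Consent before randomisation is already in the plan and needs no change.

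**Cost.** The list generator is re-run before the envelopes are printed, and two first-visit steps change order. The statistical price is slight arm imbalance within a professional's set, negligible at about 471 per arm. One list per health centre, shared by its professionals, would also break the link, but it is less practical because one envelope sequence would have to move between consulting rooms.
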